### Sample Size

An intention-to-treat method will be used to calculate sample size, considering the hypotheses for the primary outcome variables. Power calculations will be based on power determination for longitudinal designs with attrition (Hedeker et al., 1999), an alpha of 0.05, four assessment points (with baseline serving as a covariate), dropout rate of 40% and a fixed autoregressive coefficient of 0.40. A group size of 40 patients per group would provide 80% power with a bilateral *p* < 0.05 to detect a clinically significant change in eating pathology (overall Eating Disorder Examination Questionnaire, EDE-Q, of 0.45 points), assuming a standard deviation of one for the overall EDE-Q change scores (Hedeker et al., 1999), and also to detect a difference in mean weight gain of one Body Mass Index (BMI) point, which, based on previous research, would be clinically important to detect (Agras et al., 2000; Byrne et al., 2017). Therefore, if a sample loss of approximately 40% is taken into account, the participation of at least 70 participants per group will be required.

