### Outcomes

#### Patients

This study will consider primary and secondary outcomes measured at the four evaluation points: baseline (T0), post-intervention (T1), 3-month follow-up (T2) and 6-month follow-up (T3).

The following will be assessed as primary measures: ED symptomatology and psychological well-being. Secondary outcomes will include the following: body mass index (BMI), psychosocial adjustment, perfectionism, obsessive-compulsive symptomatology, motivation to change and hospital readmission. All outcomes and the instruments to be used are shown in Table 1.

**TABLE 1 T1:** Outcomes and measures/instruments.

	Outcome	Measure/instrument	References

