### Statistical Analysis

Firstly, a covariance analysis (ANCOVA) will be carried out using the pre-test scores as a covariate to analyze the impact of the combined intervention. Secondly, a repeated measures analysis of variance will be used to analyze the short and medium-term efficacy of the combined intervention in comparison to the usual intervention between and within groups at different time points, and effect size values will also be considered. Stratification will be performed in the analyses by the admission center and “diagnosis” variable will be controlled. IBM SPSS Statistics 24.0 will be used for all the analyses (IBM Corp, 2016).

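### The stated 80% power fits an arm difference pooled over the three follow-ups; the ANCOVA named first, if run at post-intervention, has about 58–66% at 40 analysed per group

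*Protocol article*

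**What the plan says.** The Sample Size section of the protocol article states: "Power calculations will be based on power determination for longitudinal designs with attrition". The inputs are "an alpha of 0.05, four assessment points (with baseline serving as a covariate"). Beyond these, it assumes that 40% are lost and fixes the autoregressive coefficient at 0.40. The difference to detect is 0.45 points on the overall EDE-Q, with a standard deviation of 1 that the text attaches to change scores. The result is given as "A group size of 40 patients per group would provide 80% power", two-sided, and the target is then raised to 70 per group for loss. The Outcomes section (Patients) defines the four assessments as "baseline (T0), post-intervention (T1), 3-month follow-up (T2) and 6-month follow-up (T3") and lists ED symptomatology among the primary measures.

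The Statistical Analysis section names two analyses. The one listed at the start is described in these words: "a covariance analysis (ANCOVA) will be carried out using the pre-test scores as a covariate to analyze the impact of the combined intervention". The other one covers the follow-up period and is described as follows: "a repeated measures analysis of variance will be used to analyze the short and medium-term efficacy of the combined intervention". It is meant to compare the arms as well as the visits inside each arm. Centre is a stratification factor and diagnosis is controlled for. Neither analysis is called primary, the visit for the ANCOVA is not given, and the text does not say whether baseline is one of the levels in the repeated-measures ANOVA.

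**The concern.** The power figure rests on three post-baseline measurements per patient. The analysis that the article assigns to the impact of the intervention reads as a single pre/post comparison, because the later time points go to the second analysis. A single visit carries less information than three visits pooled, so the 80% need not carry over.

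If it does not, a non-significant ANCOVA on the EDE-Q would be read as coming from a test with a 20% type II error when the true error is considerably larger. There is also a choice between planned tests of quite different power, and the article does not say which one decides.

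**Working it through.** **Inputs.** From Sample Size: difference 0.45, SD 1, two-sided alpha 0.05, autoregressive coefficient 0.40, baseline as covariate, 40 per group. From Outcomes: follow-ups T1, T2 and T3. The 70 per group less 40% leaves 70 × 0.6 = 42, so 42 is also shown. Power is from the noncentral t with noncentrality d / √(2V/n), where V is the residual variance of the quantity compared. I assume the same 0.45 difference at each follow-up and complete data among the n analysed.

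**1. Recovering the stated figure: baseline-adjusted mean of T1–T3, per-occasion SD 1.**
- Given baseline, the variances are 1 − 0.40² = 0.84, 1 − 0.16² = 0.9744 and 1 − 0.064² = 0.9959.
- The covariances are 0.40 − 0.40 × 0.16 = 0.336 (T1, T2), 0.16 − 0.40 × 0.064 = 0.1344 (T1, T3) and 0.40 − 0.16 × 0.064 = 0.3898 (T2, T3).
- V = [2.8103 + 2 × 0.8602] / 9 = 0.503.
- Noncentrality at n = 40: 0.45 / √(2 × 0.503 / 40) = 2.84. Power is **80.0%** (81.0% by the normal formula).

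**2. The same pooling on three change scores with SD 1 and no further adjustment.**
- V = [3 + 2(0.40 + 0.40 + 0.16)] / 9 = 0.547.
- Noncentrality 2.72. Power is **77%** at 40 and 79% at 42.

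**3. ANCOVA at T1 only, correlation 0.40 with baseline.** V = σ²(1 − 0.40²).
- Per-occasion SD 1: V = 0.84, noncentrality 2.20. Power is **58%** at 40 and 60% at 42.
- Change-score SD 1: 2σ²(1 − 0.40) = 1, so σ² = 0.833 and V = 0.833 × 0.84 = 0.70, noncentrality 2.41. Power is **66%** at 40 and 68% at 42.
- For 80% power this test needs 67 or 56 analysed per group respectively.

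**4. Between-group effect in the repeated-measures ANOVA, per-occasion SD 1.**
- T1–T3 as levels: V = 0.547, as in step 2. Power is about **77%**.
- T0–T3 as levels: the averaged difference falls to 0.45 × 3/4 = 0.3375. V = [4 + 2(3 × 0.40 + 2 × 0.16 + 0.064)] / 16 = 0.448. Noncentrality 0.3375 / √(2 × 0.448 / 40) = 2.26. Power is about **61%**.

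**5. Does the SD scale matter?** Setting the T1 change-score SD to 1 divides every per-occasion variance by 1.2. The pooled contrast of step 1 then has V = 0.503 / 1.2 = 0.420 and about 87% power, against 66% for the T1 ANCOVA. The two ANOVA figures in step 4 become about 84% (V = 0.547 / 1.2 = 0.456) and 68% (V = 0.448 / 1.2 = 0.373). The gap between the pooled contrast and the T1 ANCOVA is a little over 20 points on either scale.

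**The case against.** The strongest reply is that no stated arithmetic is wrong: the 80% reproduces for a longitudinal, baseline-adjusted contrast, and the second planned analysis is longitudinal. This largely stands. A reader might infer that the sample size calculation is in error, or that no planned analysis comes near 80%, and the document supports neither inference. If the repeated-measures ANOVA uses T1–T3 only, its between-group effect comes close. The article does not say that baseline is left out as a level, however, and it gives the pre-test a covariate role only in the ANCOVA.

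A second reply is that both ends of the mismatch are inferred. The article does not write down the powered contrast, and other routes reach a similar number: a one-sample test of 0.45 SD at 40 patients gives about 79–81%. Nor does it name the ANCOVA's visit. That is fair, and the point is conditional to that extent. But the section describes its own calculation as longitudinal with "four assessment points (with baseline serving as a covariate"), and the pooled contrast fits that description closely. Giving the later time points to a separate analysis makes T1 the natural visit for the ANCOVA.

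A third reply is that another correlation would rescue the ANCOVA. It reaches about 80% only with a correlation near 0.70 (per-occasion SD 1) or near 0 (change-score SD 1). Taking 0.40 as the baseline correlation is an assumption, but it is the only correlation the article gives.

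Finally, a reader might conclude that the first test is little better than even odds. That would rest on 51%, which is the power of an unadjusted change-score t-test, and the plan does not name that test. Very low power for a group-by-time interaction is also tempting to cite, but it depends on the variance scale, the shape of the effect and the levels used, none of which is stated.

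**Conclusion.** The mismatch holds, and the plan should be corrected. The 80% belongs to a comparison that pools T1–T3. The ANCOVA named first, read as a post-intervention comparison, has about 58–66% power at 40 analysed per group and 60–68% at 42, so its type II error at 40 is 34–42%. The repeated-measures ANOVA approaches the stated figure only through its between-group effect on T1–T3 (about 77% with per-occasion SD 1), and falls to about 61% if baseline is a fourth level.

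This rests on a T1 ANCOVA, a baseline correlation of 0.40, a constant 0.45 difference over follow-up, and reading 40–42 as patients analysed, as the increase to 70 implies. The abstract's total of 80 patients is a separate discrepancy and plays no part here. The defect is a stated power attached to a test that does not have it. It is neither an arithmetic error nor a flaw in the design.

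**What to change.** Choose one of two changes, and settle it before any outcome data are analysed by arm.

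1. In Statistical Analysis, name the baseline-adjusted arm difference in EDE-Q averaged over T1, T2 and T3 as the primary EDE-Q analysis, from one longitudinal model with baseline EDE-Q, centre and diagnosis. Keep the T1 ANCOVA as supportive. In Sample Size, state that the 80% refers to this average, and whether the SD of 1 is per occasion or for change scores.
2. If the T1 ANCOVA is the main test, say so, and replace the 80% in Sample Size with its own power: about 58–66% at 40 analysed per group under the stated assumptions.

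Either change costs only wording in these two sections, with no extra patients, visits or data. The second makes the stated power less favourable.

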## Abstract

**Introduction:** One of the major problems with inpatient treatment of adolescent girls with an eating disorder (ED) is that the strategies learned during their hospital stay are not easily applied or maintained in their daily lives, and this has been related to high rates of relapse and readmission. The ECHOMANTRA programme was developed to optimize outcomes during and following inpatient or day-patient treatment. ECHOMANTRA is based on interventions for carers (Experienced Carers Helping Others, ECHO) and patients (Maudsley Model of Anorexia Nervosa Treatment for Adults, MANTRA) and is developed from the cognitive interpersonal model of anorexia (Schmidt and Treasure, 2006; Treasure and Schmidt, 2013). This study aims to describe the study protocol of a randomized controlled trial (RCT) for evaluating the efficacy of an adaptation of a novel intervention for patients and carers (ECHOMANTRA) to be implemented as an add-on to treatment-as-usual (TAU).

**Method:** In a multi−center pilot RCT, 80 female adolescent patients with a DSM-5 diagnosis of an ED and their carers will be invited to participate in the study. They will then be randomized to receive either the ECHOMANTRA intervention as an add-on to TAU or TAU alone. A repeated measures design will be conducted across four time points. Primary outcomes will be patient psychological well-being and eating disorder symptoms, and secondary outcomes will include body mass index, obsessive-compulsive symptoms, perfectionism, motivation to change and psychosocial adjustment. For carers, outcome variables will include psychological well-being, expressed emotion, accommodation and enabling behaviors, burden, and care skills.

**Discussion:** The results from this trial will establish the effectiveness of ECHOMANTRA and may reveal whether and to what extent this novel intervention can optimize outcomes during and following inpatient treatment. This study will also provide the adaptation of the ECHOMANTRA in the Spanish context for inpatient/day-care treatment.

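### The abstract gives 80 patients, the Sample Size section requires at least 140, and the 40% dropout appears both inside and on top of the 40-per-group figure

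*Protocol article*

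**What the plan says.** The abstract of the protocol article states that "80 female adolescent patients with a DSM-5 diagnosis of an ED and their carers will be invited to participate in the study" and that they will then be randomised. Study Design and Procedure fixes 1:1 allocation, so this is 40 per group.

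The Sample Size section describes a power calculation for longitudinal designs with attrition. Its inputs are "an alpha of 0.05", four assessments with baseline as covariate, and a "dropout rate of 40% and a fixed autoregressive coefficient of 0.40". It then says "A group size of 40 patients per group would provide 80% power with a bilateral" 5% test, for a difference in "overall Eating Disorder Examination Questionnaire, EDE-Q, of 0.45 points" with a standard deviation of one for the change scores. It ends: "if a sample loss of approximately 40% is taken into account, the participation of at least 70 participants per group will be required".

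Statistical Analysis names an ANCOVA on pre-test scores and a repeated-measures analysis of variance. It does not name a mixed model.

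**The concern.** There are two recruitment totals, 80 and at least 140, and nothing in the article reconciles them. The 80 is exactly twice the 40 per group that stands before the closing inflation, which suggests that an uninflated figure went into the abstract.

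The dropout rate also enters twice. It is a listed input to the calculation that yields 40, and it is then the reason for moving from 40 to 70. If it was already in the 40, the second use is surplus. If it was not, it should not be listed as an input.

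At stake is whether the 80% power claim applies to the number the abstract announces. If it does not and recruitment stops at 80, a null result would be read as stronger evidence of no effect than the trial can give. If it does, 140 asks for 60 more dyads than the calculation needs.

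**Working it through.** **Inputs from the article.** Two-sided alpha 0.05; effect 0.45 EDE-Q points; SD 1; autoregressive coefficient 0.40; baseline as covariate with three follow-ups (T1-T3); 40% dropout; 1:1 allocation.

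**Assumptions the article does not give.** The effect is 0.45 at every follow-up; the correlation decays as 0.40, 0.16, 0.064; loss is equal in both arms. Two readings of SD 1 and two patterns of gradual loss are tried.

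**Step 1: the totals.**
- Abstract: 80/2 = 40 per group.
- Sample Size: 2 x 70 = 140, which is 60 more than 80.
- Inflating 40 evaluable for 40% loss: 40/(1 - 0.40) = 66.7, so 67 per group (134). The stated 70 is a rounding up of this.
- Evaluable numbers after 40% loss: 70 x 0.6 = 42 and 40 x 0.6 = 24 per group.

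**Step 2: reproducing 40 per group at 80%, SD 1 per visit.** Given baseline, the covariance of follow-ups i and j is 0.4^|i-j| - 0.4^(i+j). The variances are 0.840, 0.974 and 0.996; the covariances are 0.336, 0.134 and 0.390. The variance of the three-visit mean is (2.810 + 2 x 0.860)/9 = 0.503, so its SD is 0.7095. With noncentrality 0.45/(0.7095 x sqrt(2/n)) and a two-sided t test:
- n = 40: noncentrality 2.84, power 80.0%. The plan's figure is reproduced with no loss.
- n = 24: noncentrality 2.20, power 57.6%.
- n = 42: noncentrality 2.91, power 81.9%.

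**Step 3: SD 1 for the baseline-to-T1 change score.** The change variance is 2 x (1 - 0.40) = 1.2 times the per-visit variance, so the per-visit SD is 1/sqrt(1.2) = 0.913. The SD of the adjusted mean is 0.7095 x 0.913 = 0.648.
- n = 40, no loss: 86.6%.
- n = 24: 65.4%.
- n = 42: 88.2%.

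For the 24 completers, weighting visits optimally gives 58.9% (Step 2) and 66.7% (Step 3); a normal approximation gives 59.4% and 67.3%. The completer figures are therefore about 58-60% and 65-68%.

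**Step 4: 40 enrolled per arm, gradual loss, partial data kept.** Each dropout pattern contributes its share times 1'V⁻¹1, where V is the covariance of the visits it has. The inverse of the sum replaces the variance above.

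| Retention T1/T2/T3 | SD 1 per visit | SD 1 for change to T1 |
|---|---|---|
| 87/73/60% | variance 0.624, power 71% | variance 0.520, power 79% |
| 100/80/60% | variance 0.559, power 76% | variance 0.465, power 83% |

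If a mixed model estimates visit-specific effects and averages them, the first cell has variance 0.667, and the normal approximation gives 0.45/sqrt(2 x 0.667/40) - 1.96 = 0.50, or 69%. The range with partial data kept is about 69-83%.

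The BMI power statement cannot be checked, because no SD is given for it.

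**The case against.** The strongest reply is that 40 per group may already include attrition. The method is described as one for designs with attrition, and 40% is a stated input. The SD of one is also worded as that of change scores, not of scores at a visit. On that wording, 40 enrolled per arm with gradual 40% loss gives 79-83% when partial data are kept (Step 4), so the stated 80% can be reached at 80 enrolled. This stands. It would make the closing 70 per group the figure in error.

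A reader might infer that 40 gives 80% only without attrition, that 40 must therefore be complete cases, and that 80 enrolled certainly fails. The article does not support this: the exact match in Step 2 relies on taking SD 1 as per visit. If SD 1 is instead the average over the three change scores (mean variance multiplier (1.2 + 1.68 + 1.872)/3 = 1.584, per-visit SD 0.795), 87/73/60% retention gives 88.6% and completers alone about 77%. If it is the change to T3 (multiplier 1.872, per-visit SD 0.731), completers alone reach about 84%.

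Nor is 70 an error in itself. The text says approximately 40% and at least 70, so rounding 67 up is legitimate.

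Two other replies do not remove the point. Calling the trial a pilot does not, because it is also called a superiority study and makes an explicit power claim. Condensation into an article does not, because the difficulty is two incompatible printed numbers, not something left out.

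**Conclusion.** The contradiction between 80 and at least 140 is certain and rests on no modelling. So is the double appearance of the 40% dropout. At least one stated figure must change. Because the abstract speaks of 80 being invited, the number randomised could be lower still.

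Which figure is wrong is not settled. The closing sentence, with 40/0.6 = 67 taken up to 70, favours 40 as the evaluable number. The abstract's 80 would then be uninflated, and 24 evaluable per group cannot deliver the power claimed for 40.

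The size of any shortfall at 80 enrolled is conditional. With SD 1 per visit or for the change to T1, an analysis of completers gives about 58-68%. Conventional repeated-measures ANOVA would analyse completers, so this is the closer match to the named methods. With gradual loss and partial data kept in a mixed model, it is about 69-83%. These ranges assume a constant effect, equal loss in both arms and first-order autoregressive correlation. No single figure should be quoted as the power delivered.

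**What to change.** Go back to the sample-size calculation as it was run and establish whether 40 per group is the number randomised or the number evaluable. State that in the Sample Size section, count the 40% dropout once, and give the same enrolment target there and in the abstract.

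- If 40 is evaluable: change the abstract to at least 70 dyads per group (140). If only 80 will be recruited, replace the 80% claim with the power delivered under the planned analysis and dropout, and state the SD definition and loss pattern assumed.
- If 40 already allows for loss: remove the second inflation to 70 and keep 80 throughout.

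Dropout should not be struck from the list of inputs before the calculation has been checked, since that could replace a correct statement with a wrong one.

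The cost is wording, and possibly a less favourable stated power if the target stays at 80.

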### Interventions/Treatment Arms

#### Treatment as Usual

We have chosen not to use a standardized comparison treatment as this would require practical changes in different settings and resource management (including training, supervision and quality control), which will not be feasible. We have therefore chosen to allow centers to follow their own procedures for TAU. We will stratify our analyses by center, which will be adjusted accordingly for any bias.

For TAU inpatient care, the Eating Disorder Unit at the San Juan Hospital will provide a programme using a multidisciplinary team approach (dietician, psychologist, physician and nurse). It will include monitoring of physical risks, nutritional rehabilitation, education on healthy eating and nutrition patterns. Besides it will try to modify/improve thoughts, attitudes, behaviors and feelings that maintain the illness through psychological therapy. Once a patient has stabilized and reached a healthy body mass index, she is discharged. She is then either followed up to assess her progress and to facilitate transition to home or she is referred to a day care center.

Treatment-as-usual in the day care centers (ADANER and CREA) will involve multidisciplinary treatment including dietetic support, psychological interventions, school education, and when appropriate, sessions with psychiatrists. Patients will receive the following psychological interventions: weekly individual cognitive behavioral therapy for eating disorders (CBT-ED); and psychoeducational group therapy on nutrition, emotion management, body image, social skills and problem-solving strategies. Usually, patients attend every day of the week (from Monday to Friday) for an average of 6 h. They receive psychological intervention sessions and they also make the different meals of the day. Parents/carers can also access a fortnightly parent support group.

The TAU-only (control condition) group will have no access to the intervention materials or the ECHOMANTRA intervention sessions. At the end of the study, individuals randomized to the TAU-only condition will be offered the self-help components of the intervention.

#### Treatment-as-Usual Plus Patient and Carer Skills-Sharing Intervention (ECHOMANTRA)

In the experimental group, the adaptation of the ECHOMANTRA programme will be implemented. The contents of the intervention will be translated into the Spanish language and adapted to a Spanish-speaking cultural context.

##### Patients

Based on the interpersonal model of AN, the “MANTRA” part of the ECHOMANTRA intervention addresses patients’ modifiable characteristics, such as difficulties in emotional regulation, interpersonal relationships and eating. The intervention includes a workbook with an emphasis on specific behavioral change strategies. The workbook is organized into eight chapters that correspond to the contents of the eight sessions of the programme.

MANTRA will involved eight, weekly, individual online sessions lasting 60 min, which will be delivered by assistant psychologists trained by the first and principal authors of the study (YQ and [name]). During the sessions, the trained psychologist will encourage patients to reflect on the information and exercises proposed in the workbook. They will also carry out a series of activities taken from the MANTRA programme to further develop the contents included in the corresponding chapter of the workbook.

Each session will be themed following the structure of the patient workbook. Specifically, the focus of each session will be as follows: the first and second sessions will be on psychoeducation and motivation to change; the third session will be on skills to develop acceptance and self-compassion; the fourth and fifth sessions will be on skills to improve social functioning and to explore thinking styles; the sixth session will be on emotion management; and the seventh and eighth sessions will be on planning for the transition through goal setting, use of social support and implementation intentions.

For a more detailed description of the exercises, see Schmidt et al. (2014).

